#### Inclusion criteria

For all parts of the study, participants must be adults aged 18–28 and registered with the public social program (JeA) living in seven Colombian municipalities affected by the armed conflict. These 7 municipalities are part of the 170 municipalities categorized as “The Development Programs with a Territorial Approach” (PDET in Spanish) by the Havana peace agreement to prioritize social and economic development programs and are the areas most hardly hit by the armed conflict. JeA users are characterized by their low socioeconomic status, according to the National Social Services’ criteria. Many of them are victims of the armed conflict as defined by the victims’ law in Colombia. Participants who meet the inclusion criteria and present anxiety, depression, or post-traumatic stress disorder symptoms will be invited to participate in Phase 3 – piloting the mental health intervention.

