### Questionnaire instruments

We will invite all students across the selected PDET municipalities to complete the mental health and human capital survey. The following tools will be used to determine the severity of mental health symptoms and human capital outcomes. (1) *Patient Health Questionnaire – PHQ-9*, which is widely used to assess depression symptoms (28), has been validated for use in Colombia (29, 30) and with low income, limited education populations in rural areas with good results (31, 32). Its internal consistency is 0.80. (2) Anxiety will be assessed with GAD-7 (33). Its internal consistency is 0.90, sensitivity 0.92, and specificity 0.83. (3) A Post-traumatic stress disorder brief screen will also be included PC-PTSD-5 (34). It has a test–retest reliability of 0.83, sensitivity with a score of 3 has a sensitivity of 0.93 m specificity is 0.94. (4) Two questions from the Insomnia Severity Index (35, 36), with a reliability of 0,86, sensitivity of 0.87. (5) AF5 Self-Concept Questionnaire (6) Rosenberg Self-esteem scale (RSE) (37). These questionnaires are widely used by studies where the efficacy of interventions that use digital platforms are examined.

In terms of short-term/immediate assessment of the potential of the intervention to improve human capital, we will look at: school attendance (using administrative data on academic enrolment reports), educational permanence (using administrative data on academic permanence reports, every six months), and academic performance (using administrative data on academic excellence report, every six months). Based on data directly collected as part of the pilot intervention, we will also assess the short-term efficacy of the number of hours spent on average during the past academic period studying weekly, the number of hours that beneficiaries dedicate in this academic period to study weekly and the self-reported grade point average in current and past academic periods. In terms of the longer-term efficacy of the intervention, we will look at: certification (whether completed educational program, based on JeA administrative records) and formal labor market inclusion (whether working in a formal job, based on PILA Administrative Registry). Furthermore, we will also assess the efficacy of the mental health intervention on self-esteem (RSES) and self-concept (AF5).

Figure 3 summarizes the estimated length, activities, and instruments used in each of the phases.

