### Quantitative analysis of impact

Our primary aim will be to assess the impact of the intervention on our mental health and human capital outcomes. We will use regression analysis with a difference-in-differences design, which compares changes in outcomes before and after intervention measures across participants in treatment and control areas. This approach considers human capital as an outcome embodied in individuals by exploring the variation in individual knowledge (cognitive skills captured by academic performance) and individual abilities (non-cognitive skills acquired as life competencies). Thus, we will look at the magnitude of mental health-based rehabilitation on young adult students across different dimensions of mental health (depression and anxiety, fundamentally), which is considered beneficial due to human capital accumulation.

Since individual observations will be collected in different regions, we will adjust for clustered data. In the absence of treatment randomization that assures that treatment and control groups are exchangeable, this quasi-experimental design helps us to control for time-invariant differences between treatment and control areas by focusing on changes, rather than levels, in outcomes. To address bias from time-varying confounders, we will incorporate controls for time-varying factors in all analyses. We will all report the prevalence of depression, anxiety, and PTSD, along with their commodities and the effectiveness outcome, which will be the proportion of participants with a reduction in their baseline symptoms. To determine the changes in human capital, we will use both administrative and survey data that measure continued JeA program enrolment, accumulated grade point average, and self-reported hours dedicated to study. This will be carried out in STATA-19.

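### Continued JeA enrolment is constant at baseline, so its difference-in-differences estimate is an adjusted post-period comparison and does not remove fixed differences between municipalities

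*Protocol article*

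**What the plan says.** All references are to the Protocol article.

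- **Aim and model (Quantitative analysis of impact).** "Our primary aim will be to assess the impact of the intervention on our mental health and human capital outcomes". One method is given for both groups of outcomes: "We will use regression analysis with a difference-in-differences design, which compares changes in outcomes before and after intervention measures".
- **Rationale (same section).** In the absence of randomisation, "this quasi-experimental design helps us to control for time-invariant differences between treatment and control areas by focusing on changes, rather than levels, in outcomes". Controls for time-varying factors and an adjustment for clustering are also promised.
- **Human capital measures (same section).** Change is to be determined from "administrative and survey data that measure continued JeA program enrolment, accumulated grade point average, and self-reported hours dedicated to study".
- **Who can enter.** Inclusion criteria requires participants to be "registered with the public social program (JeA"); Phase 3 samples beneficiaries who are studying.
- **Other outcomes (Questionnaire instruments).** Certification, meaning completion of the educational programme according to JeA records, is a longer-term outcome. Attendance, permanence and academic performance come from administrative reports, the last two every six months. The survey also asks for "the self-reported grade point average in current and past academic periods".

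**The concern.** Difference-in-differences removes a fixed gap between areas only if that gap is visible in the pre-period measurement. Eligibility sets enrolment to the same value for every participant in both groups, so the pre-period difference is zero whatever the usual retention in each municipality. Subtracting it removes nothing.

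The article nevertheless says that the design "helps us to control for time-invariant differences between treatment and control areas by focusing on changes, rather than levels, in outcomes", in the same section that names continued enrolment as a measure of human capital. A retention result would be read as protected against permanent differences between three treatment and four control municipalities when it is not. Human capital is part of the stated primary aim, and the Discussion hopes the evidence will support adoption by government.

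The grade measure raises a smaller, separate matter. An accumulated average carries every earlier term, so the same effect on current grades yields a different estimate depending on how far students are into their programmes.

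**Working it through.** The article gives no figure for this point. Its one calculated figure, the sample size of 501, does not bear on it; only the ICC of 0.04 and the target of 170 per site are borrowed in step 4.

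**1. Algebra.** Let pT and pC be the post-period proportions in treatment and control areas.
- General form: DiD = (post_T − post_C) − (pre_T − pre_C).
- Continued enrolment, baseline 1 for all: DiD = (pT − 1) − (pC − 1) = pT − pC.
- Certification, baseline 0 for all: DiD = (pT − 0) − (pC − 0) = pT − pC. The zero is inferred from participants being students at entry; the article does not state it.

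**2. Does adjustment change this?** For enrolment the individual change is y_post − 1. Regressing it on treatment and changes in covariates gives the same treatment coefficient as regressing y_post on the same terms, because only the intercept moves. The result is a covariate-adjusted post-period comparison. Controls that vary over time do not stand in for a fixed gap.

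**3. Numerical check.** Data were simulated with 250 per group, no intervention effect and a fixed 10-point gap, and an OLS model with a treatment-by-period interaction was fitted.

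| Baseline value | Interaction estimate | Post-period difference |
|---|---|---|
| 1 (85% v 75% after) | 0.116 | 0.116 |
| 0 (30% v 20% after) | 0.088 | 0.088 |

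The two columns agree exactly. They differ from 0.10 only by sampling error.

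**4. Size.** Assume usual six-month retention of 90% in treatment and 85% in control areas, with no intervention effect. The expected estimate is 0.90 − 0.85 = 0.05. How often that is declared significant depends on the clustering adjustment. Assume 170 in each of the seven municipalities (510 v 680); extending the per-site target to the control sites is an assumption.
- Ignoring clustering: SE = √(0.9×0.1/510 + 0.85×0.15/680) = 0.0191, z = 0.05/0.0191 = 2.62, rejection about 75%.
- With the ICC of 0.04 (assumed to apply to retention): design effect = 1 + 169×0.04 = 7.76, SE = 0.0191×√7.76 = 0.053, z = 0.94, rejection about 16%. With a t reference on 7 − 2 = 5 degrees of freedom it is about 12%.

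The bias is 5 points in every case.

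**5. Accumulated GPA.** With k equally weighted earlier terms and one new term, the change in the average is (g_new − mean of earlier terms)/(k+1). An effect D on the new term therefore moves it by D/(k+1). The intervention lasts about 16 weeks, taken here as one term. The article does not give k.

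| Assumed k | Share of D shown |
|---|---|
| 1 | 50% |
| 3 | 25% |
| 5 | 17% |
| 8 | 11% |

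For a given k the noise in the change shrinks by the same factor. With D = 0.25 SD and an assumed within-person correlation of 0.5, the standardised effects are:
- k = 3 for all: 0.31 for the accumulated change, against 0.25 for one term minus the term before.
- k mixed evenly over 1 to 8: 0.24 for the accumulated change, against 0.31 for the new term minus the earlier mean.

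The problem is mainly the size and meaning of the estimate. It is not a general loss of power.

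**The case against.** **Other safeguards exist.** A reader might infer that retention is compared raw, with no other protection against non-random assignment. The documents do not support that. Control municipalities were chosen by a proximity score on characteristics such as poverty, conflict, health, living conditions, displacement and ethnicity, and time-varying controls are promised for all analyses. This stands, and the comparison should be called adjusted. But prior retention and completion are not among the listed matching variables, and neither safeguard restores the property claimed for differencing.

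**False positives.** A reader might take the 75% in step 4 as the false-positive risk. It is not the risk under this plan, which adjusts for clustering; the corresponding figure is about 16% or lower on the stated assumptions. The bias remains.

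**Certification.** It is not in the list of measures in the analysis section, and its baseline value is inferred. That stands. It is, however, a human capital outcome, and the article's general sentence gives no other model for it.

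**Registration is not the same as a clean record.** A registered student may have had a lapse in an earlier attendance or permanence report, so a pre-period could vary, and how it is built may be left to an analysis plan. That is fair for those reports. It does not rescue continued enrolment: anyone who had already left JeA cannot be in the sample, so earlier departures in each municipality remain unseen.

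**GPA.** Accumulated GPA is a legitimate outcome on its own scale, and period grades are collected as well. Both points stand, so a claim that any effect on grades is lost would go too far.

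**Pilot status.** The article calls the impact analysis preliminary. That lowers the stakes but does not make the stated rationale correct for this outcome.

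**Conclusion.** The point holds in limited form. For continued JeA enrolment, the difference-in-differences estimate is the covariate-adjusted post-period difference between non-randomised municipalities, and the stated control of fixed area differences is absent. This follows from the eligibility rule and algebra, provided enrolment is a person-level indicator of JeA registration. Certification follows if it is analysed under the same general model and everyone starts uncompleted.

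A permanent gap in retention enters the estimate one for one. The 5-point example is an assumption; the documents give no retention rates. Study hours and formal employment can vary at baseline and are not affected.

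The GPA point is secondary. The displayed effect is 1/(k+1) of the effect on one new term, assuming equal term weights, with k unknown.

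**What to change.** 1. **Wording and model for enrolment, permanence and certification.** In Quantitative analysis of impact, describe these as post-period comparisons adjusted for baseline individual covariates and, where available, each municipality's earlier retention rate from the six-monthly JeA reports. Drop the claim about fixed area differences for them. The cost is a few sentences and one further extract from an administrative source already in use. With seven municipalities, a municipality-level covariate also takes one of the five between-group degrees of freedom, so the choice should be fixed in advance.

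2. **Earlier cohorts, as support only.** A difference-in-differences on retention rates of earlier and current JeA cohorts in the same municipalities would have a real pre-period. It covers all JeA students, not only symptomatic volunteers, so it answers a different question and would dilute an effect confined to participants. It should not replace the analysis in item 1.

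3. **Grades.** Use period GPA before and after the intervention for the difference-in-differences on grades, and keep accumulated GPA as descriptive if wanted. No new data are needed. There are two downsides. Period GPA is self-reported, so the six-monthly performance reports should be used alongside it. A single prior term is also a noisier baseline than an average of several (0.25 against 0.31 in step 5 at k = 3). The gain is an estimate whose size does not depend on programme stage.

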### ‘Youth in Action’ program

The ‘Youth in Action’ program (Jóvenes en Acción in Spanish-JeA) is a major initiative of the Colombian government to decrease economic disparities by strengthening the formation of human capital among vulnerable young people living in poverty. Introduced in 2012, JeA supports young beneficiaries undertaking vocational training or university education with tuition fees and a living allowance given upon successful attendance and performance verification. JeA also offers a “skills for life” (Habilidades Para la Vida, in Spanish) training component to strengthen general skills that might increase long-term employability. The program currently hosts 445,000 beneficiaries, 14% living in conflict-affected municipalities. Although the program has been shown to impact educational outcomes and employment opportunities significantly, high levels of MHP among beneficiaries have been identified as an essential barrier to success (14).

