## The present study

This study aims to design and pilot a mental health support intervention embedded within the JeA human capital program to achieve better outcomes among beneficiaries, especially those displaced by conflict and the most socioeconomically vulnerable. We aim to develop and test the feasibility and acceptability of a mental health intervention that addresses comorbid mental health problems among beneficiaries of the JeA program. We also aim to make a first evaluation of the impact of potential mental health improvements on human capital outcomes, including educational and employment outcomes.

We will also assess the several outcomes of the mental health intervention to improve the chances of JeA beneficiaries of completing the program and building human capital. Specifically, we will assess preliminary clinical outcomes of the relationship between the mental health intervention, compared to a control group, with dimensions related to human capital formation using a combination of administrative data and survey data collected as part of the intervention, that includes data on academic performance and attendance, as well as data on employment following the completion of the program. We also assess cross-site comparisons in efficacy to see if the effect differs by region. An analysis of the most recent national mental health survey data for conflict victims has not highlighted regional differences in the prevalence of common mental health disorders for victims of the conflict (7). They underscore the need for increased mental health services for this population in their regions. Notwithstanding, we will include in our statistical analysis tests for regional differences, comparing against control groups.

The project has three main research questions leading to methodological, empirical, and policy-related contributions:

Can a stepped-care mental health with a digital component improve young people’s mental health and human capital in conflict-affected areas?Can this stepped-care mental health intervention improve young people’s chances of succeeding in their training and educational outcomes?Is a stepped-care mental health with a digital component feasible and acceptable for inclusion in the JeA program in conflict-affected areas in Colombia?

We expect to address these aims in a period of 36 months (3 years).

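### Accumulated GPA and continued enrolment are analysed as separate outcomes, so if the intervention retains students whose grades are on a worse path, the GPA contrast is biased against it

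*Protocol article*

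**What the plan says.** Under Quantitative analysis of impact, changes in human capital are to be determined from administrative and survey data on continued enrolment in the programme, "accumulated grade point average, and self-reported hours dedicated to study". The method is a difference-in-differences regression comparing treatment and control municipalities. The article says that this design controls for differences that do not vary over time, and that time-varying confounders will be handled with covariates.

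Other sections bear on how enrolment and grades are linked:
- The present study: the outcomes are assessed with a view to the intervention's capacity to "improve the chances of JeA beneficiaries of completing the program and building human capital".
- Questionnaire instruments: retention is an outcome, as "educational permanence (using administrative data on academic permanence reports, every six months", and so is certification. Grades come from two sources: "academic performance (using administrative data on academic excellence report, every six months", and, from the survey, "the self-reported grade point average in current and past academic periods".
- 'Youth in Action' program: beneficiaries receive "a living allowance given upon successful attendance and performance verification", so staying in the programme is tied to performance.

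The article does not say how GPA is defined or analysed for a student who leaves. Nor does it say that GPA is restricted to enrolled students.

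**The concern.** Enrolment is both an intended effect and, in practice, a condition for earning further grades. A comparison of post-intervention grades therefore conditions on something the intervention may change.

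Take two students with the same falling grades. The one in a control municipality leaves, and the decline stops being recorded. The one in a treatment municipality is kept by the intervention, and the decline goes on being recorded. The intervention has helped the second student, yet that student lowers the treated group's mean.

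The two safeguards named in the article do not reach this. Differencing removes stable differences between areas, and the added covariates address confounders. Neither corrects for a change, caused by the intervention, in who has a later grade. Complete administrative records would not remove the problem either, since a leaver has no new grade to record.

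At stake is the reading of one human capital outcome: a programme that succeeds at retention could appear to do nothing for grades, or to lower them.

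**Working it through.** **Figures in the article.** No retention rate, GPA standard deviation or grade-retention correlation is given. The only yardstick is the effect size under Sample size: d = 2 x f = 2 x 0.125 = 0.25, as stated. It is not tied to GPA.

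**Assumptions.** The true effect on GPA is 0, term GPA has SD 1, and the before-after correlation is 0.6. Latent propensity to stay has correlation 0.5 with stable ability and, where stated, 0.3 with the shock to the later grade. The propensity is the same in both arms; only the share staying differs. Retention, control v treated: 90% v 95%, 80% v 90%, 70% v 85%.

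**Formula.** With drop-out p and z its normal quantile, the mean propensity among stayers is lambda = phi(z)/(1-p). A quantity with loading k on the propensity has mean k x lambda among stayers. The spurious effect is k x (lambda treated - lambda control).

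Loadings:
- later grade, through ability: sqrt(0.6) x 0.5 = 0.387
- later grade, through the shock: sqrt(0.4) x 0.3 = 0.190
- within-person change: ability cancels, leaving 0 without the shock link and 0.190 with it
- later grade, both routes (unbalanced sample): 0.387 + 0.190 = 0.577

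| Retention, control v treated | lambda control | lambda treated | Difference | Within-person, level only | Within-person, with shock | Unbalanced, level only | Unbalanced, with shock |
|---|---|---|---|---|---|---|---|
| 90% v 95% | 0.195 | 0.109 | -0.086 | 0 | -0.016 | -0.033 | -0.050 |
| 80% v 90% | 0.350 | 0.195 | -0.155 | 0 | -0.029 | -0.060 | -0.089 |
| 70% v 85% | 0.497 | 0.274 | -0.222 | 0 | -0.042 | -0.086 | -0.128 |
| 85% v 85% | 0.274 | 0.274 | 0 | 0 | 0 | 0 | 0 |

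Simulation of the same model gives the same values to within 0.001.

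**Leavers frozen at their last average.** Their change is set to 0, so each arm's mean change is 0.190 x phi(z), taking average change as 0. The differences are:
- 90% v 95%: 0.190 x (0.103 - 0.175) = -0.014
- 80% v 90%: 0.190 x (0.175 - 0.280) = -0.020
- 70% v 85%: 0.190 x (0.233 - 0.348) = -0.022

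The sign is the same and the size smaller. Freezing biases downward when the extra retained students' grades are actually falling. If their grades were rising, it would not.

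**Accumulation.** The figures above treat GPA as a single-term grade. With one earlier term, accumulated GPA moves by (new - old)/2, so the within-person figures halve, to about -0.008 to -0.021.

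**Against d = 0.25.** 0.016/0.25 = 6% and 0.042/0.25 = 17% within-person; 0.128/0.25 = 51% at the unbalanced extreme.

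**The case against.** A reader might infer that GPA can be observed only for students still enrolled. The article does not say so. An accumulated average exists up to the last completed term, the survey collects self-reported grades for current and past periods, and leaving the cash-transfer programme need not mean leaving the institution. This objection stands, but it does not dispose of the point: a frozen average still omits the later decline, and a grade for the current period has no meaning for someone no longer studying.

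A second inference would be that the bias must occur and must be a large share of the planned effect. That is not supported either. It requires unequal retention and, for within-person change, leaving related to grade trajectory rather than only to level. The performance condition on the allowance makes performance-related leaving plausible but says nothing about trajectory. The intervention lasts about 16 weeks and the last survey comes three months after endline, so roughly one six-monthly report falls in that window. A large retention gain may be optimistic.

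Third, the handling of leavers could sit in an analysis plan not shown here, and enrolment is reported anyway, so readers would see a retention difference. That is fair as regards missing-data detail. It does not meet the structural point, which comes from the outcomes and the estimator family that the article itself fixes: seeing two separate estimates does not tell the reader how one distorts the other.

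**Conclusion.** The point holds in conditional form. Treating accumulated GPA and continued enrolment as parallel outcomes leaves the GPA contrast open to bias against the intervention if it keeps students whose grades are on a worse path. The planned differencing and covariates do not deal with this.

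Under the stated assumptions the within-person bias ranges from 0 to about -0.04 SD, less for an accumulated average. With an unbalanced sample it reaches about -0.13 SD. It vanishes when retention is equal between arms. The article fixes neither the sample for this regression nor the rates, so the size is illustrative; the direction follows only under the condition named.

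The documents do not support reading this as an analysis confined to enrolled students, or as grounds for replacing GPA as an outcome. It is a worthwhile, low-cost improvement to one of several human capital outcomes in a pilot.

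**What to change.** In Quantitative analysis of impact, keep GPA as an outcome and add the following:
1. Report the GPA result jointly with retention in each arm and the difference between arms.
2. Add a sensitivity analysis defined for everyone enrolled at baseline, for example a rank outcome with drop-out without certification placed lowest, and/or trimming (Lee-type) bounds for differential retention. The permanence, performance and certification records already planned are enough. A pass/fail version would need a field that the article does not list.
3. State that a GPA difference is not to be read as harm or lack of benefit when retention differs between arms.

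The cost is a little more analysis and wider intervals. A rank outcome with drop-out lowest also answers a somewhat different question and overlaps with permanence and certification, which is why it belongs in a sensitivity analysis. Because municipalities are not randomised, the bounds need added assumptions, to be stated: retention moves in one direction only, and trends are comparable between areas.
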